## Study AIMS

### General and specific aims

The *2-Brain Regulation to Achieve Improved Neuroprotection during Early Development* (2-BRAINED) research project is funded by the Italian Ministry of Health under the Ricerca Finalizzata 2021 program (research line: Giovani Ricercatori, project code: GR-2021-12375213). It is aimed to assess brain-to-brain co-regulation patterns in dyads of VPT infants and their caregivers and further explore how an early VF intervention may facilitate specific inter-brain regulatory indices.

The first specific aim (Aim 1) is to assess the presence of statistically significant differences in a set of brain-to-brain co-regulation indices—primarily, PLV measure—between dyads of caregivers and VPT compared to FT infants. Previous research gave evidence of specific markers of lower co-regulation in behavioral synchrony (Montirosso et al., 2010), physiological coupling (Feldman and Eidelman, 2007; Porges et al., 2019), and neuroendocrine attunement (Provenzi et al., 2019) in dyads of VPT infants during the first year of life. Consistently, we hypothesized that VPT infants and their caregivers would show less strong brain-to-brain co-regulation indices compared to dyads of FT counterparts at 9 months (corrected age for prematurity, CA).

The second specific aim (Aim 2) is to investigate the effect of an early VF intervention for parents of VPT infants on the selected indices of brain-to-brain co-regulation at 9 months CA. By comparing EEG-hyperscanning-derived indices of inter-brain coupling between dyads of VPT infants exposed to the VF intervention and dyads exposed to care as usual during the 3 months following NICU discharge, we hypothesize to describe greater brain-to-brain co-regulation in the former group.

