
#### Estimating indices of inter-brain co-regulation

Several inter-brain synchronization indices have been proposed so far to estimate the coupling between two brains (Czeszumski et al., 2020). Since there is still debate on the appropriateness of each inter-brain synchronization measure, we plan to compute and compare several indices (see Table 4). To further check for spurious findings and gather stronger evidence that the obtained co-regulation estimations are not artifact production, we will compare the synchronization indices obtained from the real dyads to surrogate data generated by randomly pairing mothers and infants from different dyads.

**Table 4 tab4:** Indices of inter-brain co-regulation adopted in the 2-BRAINED study.

Index	Description	Notes	Reference
Phase-Locking Value (PLV)	Frequency-specific transients of phase locking independent of amplitude. The value ranges from 0 to 1: values closer to 0 indicate random signals with unsynchronized phases; values closer to 1 indicate stronger coupling between the two signals.	While previous studies focused mainly on infant frequency bands, cross-frequency PLV indices will be obtained for the purposes of the 2-BRAINED study.	Lachaux et al. (1999); Canolty and Knight (2010)
Imaginary Coherence (ICoh)	Computed through spectral density (power) of each participant and cross-spectral density between them to estimate the average phase difference and consistency of phase difference synchronization.	ICoh is expressed as a complex number: the real part represents how much the coherence is driven by instantaneous interactions; the imaginary part shows how much the coherence is based on lagged interactions.	Dikker et al. (2021); Turk et al. (2022)
Amplitude-Amplitude Coupling (AAC)	Expressed as Pearson’s correlation coefficient between normalized power time courses of the two signals.	Amplitude coupling was suggested as a valid alternative to phase coupling for three main reasons: amplitude changes are more easily estimated; amplitude modulations are more extensively characterized across EEG studies; amplitude modulations are more sensitive to neural coupling phenomena non-detectable with other phase-related measures.	Haresign et al. (2022); Koul et al. (2023)

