The computation of synchronization measures will preferentially occur considering homologous channels for the sake of interpretability and computational costs. However, as an exploratory analysis, we will also compute synchronization between non-homologous channels because we can hypothesize that synchronization tasks between mother and infant can involve different brain areas in the two actors (Endevelt-Shapira et al., 2021).

Regarding the frequency bands on which the synchronization measures will be computed, we will mainly consider alpha and theta. Indeed, these frequencies have been found to be involved in parent–infant social tasks, with theta fluctuations linked to changes in shared attention during joint play of parent and infant (Wass et al., 2018), enhancement of alpha and theta power linked to changes in directed gaze (Leong et al., 2017), and fluctuations in alpha band linked to changes in emotional states of mother and child (Santamaria et al., 2020).

Moreover, since we are interested in the dynamic evolution of brain-to-brain synchronization, we plan to evaluate the trend of each synchronization index over time (i.e., over the epochs). In particular, we are interested in the change between an asynchronous to a synchronous state, which is defined as reparation. Reparation is a dyadic process in which unmatched dyadic states are transformed into matched dyadic states. We will compute the rate and the latency of reparation considering the EEG synchronization indices as previously performed in synchronized behaviors assessment (Provenzi et al., 2015).

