### Statistical power and sample size estimates

The sample size has been estimated according to over-arching Aim 2, setting parameters as follows: medium effect size, *f* = 0.25, *alpha* = 0.05, *beta* = 0.20, number of groups = 3 (VPT-VF, VPT-CU, and FT). The procedure yielded a total sample size of 159 subjects (53 subjects per RCT arm). Nonetheless, considering the longitudinal nature of the study and the attrition rate related to EEG tasks with infants, an oversampling of *n* = 80 (~ +50%) subjects per RCT arm was planned to secure the minimum sample size for appropriately powered statistical analyses.

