### Plan of statistical analyses

#### Preliminary analyses

##### Specific aim 1

General linear models (GLMs) will be carried out to compare VPT and FT dyadic brain-to-brain co-regulation indices during the experimental procedure phases. Theoretically relevant (e.g., gestational age) and statistically identified (e.g., any variable significantly linked with the outcome variables) confounding variables will be controlled for in the analytical model.

##### Specific aim 2

Separate analyses of variance (ANOVA) will be used with dyadic brain-to-brain co-regulation indices as the dependent variable and groups (FT, VPT-VF, and VPT-CU) as the independent variable. Theoretically relevant (e.g., gestational age) and statistically identified (e.g., any variable significantly linked with the outcome variables) confounding variables will be controlled for in the analytical model.

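### Aim 2 is sized as one three-group test at 5%, but PLV alone, the main index, allows two to six such tests, and no VPT-VF versus VPT-CU comparison is named as primary

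*Protocol article*

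**What the plan says.** Under the statistical power heading, the sample size is tied to Aim 2 with "medium effect size, *f* = 0.25, *alpha* = 0.05, *beta* = 0.20, number of groups = 3". This gives 159 dyads, 53 per arm, raised to 80 per arm for attrition. It is the calculation for one omnibus test.

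Under the plan of statistical analyses, Specific aim 2, the method is plural: "Separate analyses of variance (ANOVA) will be used with dyadic brain-to-brain co-regulation indices as the dependent variable". The independent variable is the three-level group (FT, VPT-VF, VPT-CU), with adjustment for confounders. No follow-up contrast between the two randomised arms is stated.

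On the outcome side:

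- The aims section refers to "a set of brain-to-brain co-regulation indices" with PLV foremost, under Aim 1. The abstract treats the remaining indices as explorative. Aim 2 refers to selected indices in the plural and does not restate a primary one.
- The section on inter-brain indices says "we plan to compute and compare several indices". Table 4 lists PLV, imaginary coherence (ICoh) and amplitude-amplitude coupling (AAC), and adds that PLV will also be obtained across frequencies.
- On bands it says "we will mainly consider alpha and theta", and ranks neither above the other.
- The pre-processing section splits each recording into Play, Still-Face and Reunion. Specific aim 1 compares groups during these phases. Specific aim 2 does not mention them.
- Reparation rate and latency are added. Non-homologous channel pairs are already labelled exploratory.

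**The concern.** The sample size allows one test at 5%. The analysis, followed as written, produces several, and the article does not say which one decides whether video-feedback worked. Ranking PLV above the other indices helps but does not settle the matter, because PLV is itself a family of values by band and possibly by episode.

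There is a second gap. The test that was sized is a three-group F that includes the non-randomised FT group, whereas the Aim 2 hypothesis concerns the two randomised arms. A significant F can come entirely from the FT group.

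At stake is the confirmatory standing of the main result. If one band or episode turns out favourable, a reader cannot tell whether it was the planned test, and the 5% level behind the 159 dyads does not attach to the claim.

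**Working it through.** **Step 1. Reproduce the plan's figure.** Inputs from the sample size section: f = 0.25, alpha 0.05, power 0.80, three equal groups. For a one-way ANOVA the noncentrality is λ = N·f². The smallest N reaching 80% power is 158, which becomes 53 per arm, or 159. At N = 159, λ = 159 × 0.0625 = 9.94 on 2 and 156 degrees of freedom, and power is 0.805. Oversampling: 53 × 1.5 = 79.5, so 80. The figure is reproduced, and it is for exactly one F test.

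**Step 2. Count the tests the text allows.** PLV in two bands gives 2. Two bands in Play and Reunion gives 4. Two bands in all three episodes gives 6. Adding ICoh and AAC gives 3 × 2 × 3 = 18.

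**Step 3. Chance of at least one false-positive omnibus F.** For independent tests this is 1 − 0.95^m. For correlated tests it was simulated with 53 per arm, all groups equal, a common correlation ρ between outcomes, and 8,000 replicates. The documents give no correlation, so ρ is an assumption and a range is shown.

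| Tests counted | m | Independent (formula) | ρ = 0.5 | ρ = 0.9 |
|---|---|---|---|---|
| PLV, two bands | 2 | 9.8% | 9.0% | 6.7% |
| PLV, two bands × Play and Reunion | 4 | 18.5% | 15.1% | 9.8% |
| PLV, two bands × three episodes | 6 | 26.5% | 20.4% | 11.9% |
| All three indices × two bands × three episodes | 18 | 60.3% | 40.9% | 15.8% |

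**Step 4. From the omnibus F to a video-feedback claim.** The same simulation counted false VPT-VF versus VPT-CU differences at 5%, accepted only where the omnibus F for that outcome was also significant:

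- All three groups equal: for m = 2, 4.7% (ρ = 0), 4.8% (ρ = 0.5) and 3.3% (ρ = 0.9). For m = 6, 14.7%, 10.7% and 6.2%.
- FT differs by an assumed 0.5 SD and the two preterm arms are equal: for m = 6, 25.0% (ρ = 0) and 20.4% (ρ = 0.5). For a single test, 5.3% and 4.9%. Two independent bands would give about 1 − (1 − 0.053)² = 10%.

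If the contrast is not gated by the F, the rates with all groups equal and ρ = 0.5 are 8.9% (m = 2) and 20.0% (m = 6).

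So the omnibus F protects the contrast when FT resembles the preterm groups. It protects little when FT differs, which is what Aim 1 hypothesises.

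**The case against.** The strongest reply has four parts.

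First, the article does set a hierarchy: PLV leads and the rest are explorative. This stands. It means that the 18-test row is not the error rate of the planned claim. A reader might infer a 27–60% chance of falsely declaring video-feedback effective. The documents do not support that. The range needs independent tests, although all values come from one recording per dyad. It treats a three-group F as a video-feedback claim. Its upper end counts ICoh and AAC as confirmatory.

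Second, splitting by episode is written only for Aim 1. This also stands. The six-test figure is conditional, and a reader should not conclude that Aim 2 ignores the repeated measurement of each dyad. Its text does not say whether episodes are tested separately, pooled or modelled together.

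Third, 5% per ANOVA is not stated. That is right: it is inferred from the only level given.

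Fourth, this is a condensed article, and an unseen analysis plan may contain a multiplicity rule. The absence of such a rule is therefore not the point. The point is what the article does state: a sample size for one test beside an analysis made of several. A later plan would have to reconcile the two.

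**Conclusion.** The concern holds in a limited form. The published Aim 2 analysis does not match the single test it was sized for, and neither the PLV summary nor the contrast that carries the video-feedback claim is fixed.

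For PLV alone, at an inferred 5% per test, the chance of at least one false-positive omnibus F is about 10% if only the two bands are tested. It rises to about 26% if each band is also tested in three episodes, assuming independence. Correlation lowers this, to about 20% for six tests at ρ = 0.5. It is higher only if explorative results are also used for the claim.

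The rate of a false VPT-VF versus VPT-CU claim depends on an unstated rule. In the PLV scenarios examined it runs from below 5% (two bands, gated by the F, all groups equal) to about 25% (six independent tests, FT different). The defect should be corrected, but it does not undermine the design.

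**What to change.** Before unblinding, name one primary Aim 2 test:

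- **Outcome:** PLV over the homologous target channels, in one pre-named band, with one pre-named episode summary. A mixed model with group, episode and a dyad random effect is one way to obtain it. The choice of band and episode belongs to the investigators, since the article motivates theta and alpha equally.
- **Test:** the VPT-VF versus VPT-CU contrast at 0.05.
- **Second band:** tested next in fixed order, or alpha split between the bands.
- **Everything else:** ICoh, AAC, cross-frequency, non-homologous and reparation results stay exploratory and outside the efficacy claim. For ICoh, AAC and non-homologous pairs this largely confirms what the article already says.

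The cost is plan wording, and only one PLV summary then carries the confirmatory claim. Fixed order spends no alpha. Splitting alpha equally over two bands lowers the power of the 159-dyad F test to 0.72, and 80% would need about 189 analysable dyads of the 240 enrolled (79%, against 159/240 = 66% now). Bonferroni over six tests would give 0.57.

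The 159 was sized for the three-group F, so power should be restated for the named contrast. With 53 per arm and an assumed difference of 0.5 SD, a two-group comparison has power of about 0.73.

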### Sources of bias and mitigation strategies

The heterogeneity of VPT infants’ conditions should not be underestimated. Even in the absence of severe comorbidities and brain injuries, the experience of NICU hospitalization might be very different for each infant and their parents. To avoid extreme variations, the gestational age range will be constrained between 28 and 35 weeks. Moreover, stress related to the NICU environment will be evaluated and quantified with a well-validated questionnaire (Miles et al., 1993). Selection issues might affect random allocation plans in RCT arms. The allocation to VPT-VF and VPT-CU arms will occur by using an automatically generated list of binary codes that will be consecutively matched with the enrolled families across consecutive sampling. This will reduce the risk of self-selection. To further avoid confounding by infant sex and assure sex distribution balancing, the random allocation will be stratified by infant sex by *post-hoc* controls every 20 enrollments. Parental gender will also be unconstrained, inviting the primary caregiver—and not explicitly the mother—to participate in the study, VF intervention, and observational procedures. EEG procedural steps and artifacts might easily result in the loss of subjects in a longitudinal study; a 50% oversampling was planned to achieve the minimum sample size for adequately powered statistical analyses.

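### The stated ANOVA and GLM conventionally assume one residual variance across full-term and preterm dyads; if the variances differ, either the VF versus care-as-usual contrast or the VPT versus FT test is somewhat anti-conservative

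*Protocol article*

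**What the plan says.** Under Specific aim 2 in the Plan of statistical analyses, the protocol article states: "Separate analyses of variance (ANOVA) will be used with dyadic brain-to-brain co-regulation indices as the dependent variable", and lists "groups (FT, VPT-VF, and VPT-CU) as the independent variable". The General and specific aims section defines Aim 2 more narrowly, as VPT dyads given VF against VPT dyads given care as usual. No contrast or error term for that comparison is named.

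Under Specific aim 1: "General linear models (GLMs) will be carried out to compare VPT and FT dyadic brain-to-brain co-regulation indices during the experimental procedure phases". The VPT group there is not limited to untreated dyads, so with equal arms it is about twice the size of the FT group. Both models adjust for covariates such as gestational age.

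The sample size section uses "medium effect size, *f* = 0.25, *alpha* = 0.05, *beta* = 0.20, number of groups = 3 (VPT-VF, VPT-CU, and FT" and reports: "The procedure yielded a total sample size of 159 subjects (53 subjects per RCT arm".

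The eligibility section requires FT infants to be healthy and without evident neurodevelopmental risk. The section on sources of bias warns against underestimating the heterogeneity of VPT infants and says that, even without severe morbidity, "the experience of NICU hospitalization might be very different for each infant and their parents". It also limits gestational age to 28 to 35 weeks. No section gives a standard deviation of any co-regulation index, overall or by group.

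**The concern.** An ordinary ANOVA or GLM estimates a single residual variance from all dyads in the model. That matters in two places.

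- **VF versus CU.** If this contrast is read from the three-group model in the usual way, a third of its error estimate comes from FT dyads, who were not randomised and take no part in the comparison. If FT dyads vary less than VPT dyads, the standard error is too small. If they vary more, it is too large.
- **VPT versus FT.** With about two VPT dyads to each FT dyad, pooling overstates the standard error when the larger group has the larger variance, and understates it in the opposite case.

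So whenever the two variances differ, one of the two main comparisons has a type I error above 5% and the other is conservative. The three-group omnibus F is robust at equal group sizes, but it does not isolate VF from CU.

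**Working it through.** **Reproducing the plan's figure.** One-way ANOVA, k = 3, f = 0.25, alpha 0.05, noncentrality N × f². The smallest N with power of at least 0.80 is 158 (power 0.802). Rounding up to equal arms gives 159, with noncentrality 159 × 0.0625 = 9.94 and power 0.805. The stated 159 (53 per arm) is correct.

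**Inputs for the check.** 53 dyads per group (sample size section), hence 106 VPT against 53 FT for Aim 1. Assumption: the ratio r of VPT to FT outcome variance, which the article does not give. It is taken as 0.5 to 3, with FT variance set to 1, both VPT arms at r, normal outcomes and no covariates.

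**Formulas.** The pooled variance is (2r + 1)/3.

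- VF-CU: the true squared SE is r × 2/53 and the pooled one is (2r + 1)/3 × 2/53. Pooled/true SE = sqrt((2r + 1)/(3r)).
- VPT-FT: the true squared SE is r/106 + 1/53 = (r + 2)/106 and the pooled one is (2r + 1)/3 × 3/106. Pooled/true SE = sqrt((2r + 1)/(r + 2)).
- Actual type I error = 2 × P(Z > 1.96 × SE ratio).
- VPT-FT power = P(Z > 1.96 × SE ratio − 2.802), for a difference that gives 80% power with the correct SE (1.960 + 0.842 = 2.802).

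| r (VPT/FT variance) | VF-CU SE ratio | VF-CU type I error | VPT-FT SE ratio | VPT-FT type I error | VPT-FT power |
|---|---|---|---|---|---|
| 0.5 | 1.155 | 2.4% | 0.894 | 8.0% | 85% |
| 1 | 1.000 | 5.0% | 1.000 | 5.0% | 80% |
| 1.5 | 0.943 | 6.5% | 1.069 | 3.6% | 76% |
| 2 | 0.913 | 7.4% | 1.118 | 2.8% | 73% |
| 3 | 0.882 | 8.4% | 1.183 | 2.0% | 69% |

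At r = 0.5 the 85% power is bought with the 8.0% error rate.

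**Simulation checks.** With 20,000 runs at r = 1.5, 2 and 3, VF-CU gave 6.7%, 7.4% and 8.7%, VPT-FT gave 3.9%, 2.5% and 1.9%, and the omnibus F 5.0% to 5.3%. At r = 0.5 VF-CU gave 2.5% and VPT-FT 8.0%. A separate simulation with 100,000 runs per setting, indexed by SD ratio, agrees. At SD ratio 1.25 (r = 1.56) VF-CU is 6.6% and VPT-FT 3.4%. At SD ratio 1.5 (r = 2.25) they are 7.5% and 2.6%. The omnibus F stays at 5.0% to 5.4% for SD ratios 0.8 to 2.

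**Effect of the remedy.** In the second simulation, taking the VF-CU error from the two VPT arms alone gives 4.9% to 5.0% at every ratio. Welch's test for VPT-FT gives 4.9% to 5.1%. With equal variances, VPT-FT power is 79.7% pooled and 79.4% with Welch.

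**Gating on the omnibus F.** If VF-CU is tested only after a significant omnibus F, its error under the global null is 3.4% to 4.6% for SD ratios 1.25 to 2. When FT truly differs from VPT, which is what Aim 1 hypothesises, the gate protects little: 6.4% to 8.4% in the case simulated.

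**The case against.** A reader might infer that the VF-CU test is too liberal and that the VPT-FT test loses power. The document does not support that as a statement of fact. No variance is reported, and the heterogeneity passage concerns clinical conditions and NICU experience, not the spread of phase-locking values at 9 months. That index is bounded between 0 and 1 and is expected to be lower in VPT dyads; a lower mean on a bounded scale can come with a smaller variance. The sign is therefore open, and the table shows that both directions reverse when r is below 1.

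Several further points carry weight:

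- The 28 to 35 week limit, the exclusion of major brain lesions and other morbidity, and covariate adjustment may all narrow a variance gap.
- Mixing treated and untreated dyads in Aim 1 adds only δ²/4 to the VPT variance, where δ is the VF effect in within-arm SDs: about 6% at δ = 0.5. Reaching r = 1.5 that way would need δ of about 1.4.
- The omnibus F is the only Aim 2 test named, and it holds its level.
- Robust errors and contrast details are commonly left to an analysis plan, which is not shown, so their absence is not in itself an error.

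What remains is a stated design choice. FT dyads are in the model for a question that concerns only randomised VPT dyads, and the VF-CU contrast must be read from somewhere. Covariate adjustment shifts means; it does not give the groups separate residual variances. The gestational age limit is offered to avoid extremes, not to make VPT dyads as uniform as FT dyads.

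**Conclusion.** The point holds in conditional form and is minor. Equal residual variance across FT and VPT dyads is doubtful on the protocol's own description, but neither the size nor the direction of a difference can be read from it. For an assumed VPT/FT variance ratio of 1.5 to 3, a VF-CU contrast with the pooled three-group error has a type I error of about 6.5% to 8.4%. The VPT-FT test then runs at about 3.6% to 2.0%, with power of 76% to 69% against 80% for an unequal-variance test. At ratio 0.5 the VF-CU error is about 2.5% and the VPT-FT error 8.0%. At ratio 1 nothing changes.

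These figures assume 53 per group, normal outcomes, no covariates, a single two-sample comparison for Aim 1, and a VF-CU contrast taken conventionally from the ANOVA. The 80% baseline for Aim 1 is also assumed, since the trial was sized on Aim 2. The omnibus F and the sample size of 159 are not in question.

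**What to change.** State that the VF-CU difference will be estimated with its error taken from the two randomised VPT arms only, for example by fitting the same adjusted model to VPT dyads alone. State that VPT versus FT will use heteroscedasticity-consistent (HC3) standard errors, or Welch's test when unadjusted. The three-group ANOVA can remain as a descriptive overall test.

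This takes one or two sentences and a model option, and it works whichever group is more variable. If variances are in fact equal, the loss is negligible: at 53 per group the unadjusted VF-CU error degrees of freedom fall from 156 (159 − 3) to 104 (106 − 2), and VPT-FT power changes from 79.7% to 79.4%. No change to recruitment is needed.

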**Methods and analysis:**

VPT and FT dyads will be enrolled at birth, and the former will be randomly allocated to one of two arms: VF intervention or care as usual. Short-term effectiveness will be assessed through ratings of mother–infant interaction videotaped before and after the VF intervention or care as usual. Mothers of VPT and FT infants will report on their mental state, parenting stress and bonding, and infant temperament and sensory profile at 3 and 6 months (corrected age, CA). At 9 months CA, all dyads will participate in a lab-based EEG-hyperscanning paradigm to assess brain-to-brain co-regulation through phase-locking value (PLV) and other explorative indices.

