#### VF intervention

##### Remote videotaping

Before (T1) and after (T2) the VF intervention sessions for participants allocated to VPT-VF—and at the same timepoints for participants allocated to VPT-CU—a 15-min mother–infant interaction will be videotaped remotely. Before videotaping, mothers will be asked to position the webcam or smartphone to have the widest possible view of the play area and see the entire body of both the mother and the infant. The interaction paradigm includes 10-min unrestrained face-to-face play followed by a 6-min FFSF procedure (Tronick et al., 1978) as described here: During the 2-min Play episode, mothers will be asked to play with the infant as they usually do (e.g., the infant can stay in an infant seat or on a carpet); during the 2-min Still-Face episode, mothers will be asked to interrupt any communication and maintain a still, poker face while keeping eye-contact with their infant; unconstrained interaction will be resumed during the 2-min Reunion episode.

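### Aim 2's three-group ANOVA cannot, in its ordinary form, carry the T1 interaction rating or PSS-NICU, which are described for VPT dyads only; the VF-CU contrast should be fitted in the VPT arms with T1 fixed as a covariate

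*Protocol article*

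**What the plan says.** The Aim 2 hypothesis (General and specific aims) compares co-regulation indices "between dyads of VPT infants exposed to the VF intervention and dyads exposed to care as usual". That is the randomised comparison of two arms. The model under Plan of statistical analyses, Specific aim 2, is an ANOVA with "groups (FT, VPT-VF, and VPT-CU) as the independent variable". Variables judged theoretically relevant enter as covariates, and in addition "statistically identified (e.g., any variable significantly linked with the outcome variables) confounding variables will be controlled for in the analytical model".

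On what is measured before the intervention:

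- EEG is recorded once, at T4 (Study timeline), so the outcome has no baseline value.
- VF is delivered between T1 and T2 (Study timeline).
- Mother-infant interaction is rated from sessions "videotaped before and after the VF intervention or care as usual" (Abstract). Remote videotaping describes this for the VF arm and "at the same timepoints for participants allocated to VPT-CU". No T1 taping of FT dyads is described.
- Table 2 marks the PSS-NICU as a T1 measure for VPT only. Every other questionnaire shown there starts at T2, after VF.
- Demographic and neonatal chart variables (Measures) are also pre-intervention and are not restricted to VPT.

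The sample size rests on "medium effect size, *f* = 0.25, *alpha* = 0.05, *beta* = 0.20, number of groups = 3", which gives a "total sample size of 159 subjects (53 subjects per RCT arm").

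**The concern.** The model and its covariate rule do not fit together. The rule can select any variable associated with the outcome. The PSS-NICU is a plausible candidate, since the exploratory aims name NICU-related stress as a possible moderator of caregiver EEG activity, with consequences for co-regulation. Yet it is absent by design for one of the model's three groups, and so is the T1 interaction rating. Under ordinary fitting with listwise deletion, selecting either would remove the whole FT arm, and a data-driven covariate choice would change which groups are compared. The article describes no exception, special coding or VPT-only model.

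The second stake is precision. The T1 rating is the only pre-intervention measure of interaction described, and it is available in both randomised arms. A three-group model in its ordinary form leaves it unused on the contrast that Aim 2 is about.

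**Working it through.** **1. The plan's own figure.** One-way ANOVA, three equal groups, noncentral F with df = 2 and N - 3 and noncentrality f²N, where f = 0.25 and alpha = 0.05. Power is 0.797 at N = 156 and 0.805 at N = 159. The stated 159 (53 per group) is reproduced.

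**2. What f = 0.25 implies for VF versus CU.** It does not fix the difference; that depends on the pattern of the three means.

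- Two-group equivalent: d = 2f = 0.5.
- Evenly spaced means -a, 0, +a (in SD units): f = a√(2/3), so the adjacent difference is a = 0.25 × √1.5 = 0.306.

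Power of the unadjusted VF-CU comparison at 53 per arm (noncentral t, noncentrality d√(n/2), df = 104):

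- d = 0.5: 0.5 × √26.5 = 2.574, power 72.2%. With the error variance pooled over three groups (df = 156) it is 72.5%.
- d = 0.306: power about 35%.

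For 80% power at d = 0.5, the normal approximation gives 2 × (1.960 + 0.842)²/0.25 = 62.8, that is 63 per arm.

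**3. Adding the T1 covariate in the two VPT arms.** If the covariate correlates r with the 9-month index, the residual variance is multiplied by 1 - r². The noncentrality becomes d√(n/2)/√(1 - r²) with df = 103, and the equivalent unadjusted size is 53/(1 - r²). With d = 0.5:

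| r (assumed) | Variance removed | Equivalent n per arm | Power |
|---|---|---|---|
| 0 | 0% | 53.0 | 72.2% |
| 0.1 | 1% | 53.5 | 72.7% |
| 0.2 | 4% | 55.2 | 74.0% |
| 0.3 | 9% | 58.2 | 76.2% |
| 0.4 | 16% | 63.1 | 79.5% |
| 0.5 | 25% | 70.7 | 83.8% |

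At d = 0.306 the same adjustment moves power only from 34.5% to 37.3% (r = 0.3) or 39.9% (r = 0.4).

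**4. Can the three-group model be rescued?** Yes, with special coding. Centre the covariate within VPT and set it to 0 in FT; all three groups then stay in. In 4,000 simulated trials per value of r (d = 0.5, 53 per group), power for VF-CU was:

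| r | Three groups, nested covariate | VPT arms only |
|---|---|---|
| 0.2 | 74.4% | 74.3% |
| 0.3 | 74.9% | 75.6% |
| 0.4 | 77.3% | 78.8% |
| 0.5 | 80.6% | 82.9% |

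From r = 0.3 upward the nested form recovers less, because its residual variance is pooled with unadjusted FT dyads.

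**The case against.** Four points on the other side have weight.

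- **The gain may be close to nil.** The T1 rating is behavioural and is taken at NICU discharge; the outcome is an EEG index at 9 months corrected age. The article itself reports only limited evidence that interactive behaviour and EEG signals correlate, and calls behaviour-physiology coupling in VPT dyads debated. This stands. It is why the low correlations belong at the front, and why d and r are both stated as assumptions.
- **Covariate choice is normally left to the SAP.** True of naming a prognostic covariate. But the article does fix a three-group model and an open, significance-based selection rule, and those two can collide as written.
- **T1 may not be a clean baseline.** Families are enrolled within 48 hours of birth, and the allocation list is matched to families consecutively as they enrol (Sources of bias and mitigation strategies). T1 therefore appears to follow allocation. The T1 clips are also the material reviewed in the VF sessions, so a mother who knows her arm might behave differently on camera. This stands as a caution and is carried into the fix.
- **No single T1 score is defined.** The detailed coding scheme is described for the laboratory procedure. The remedy needs one score to be named.

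**Conclusion.** The point holds in a limited form. The only pre-intervention interaction and psychological measures that the article describes are VPT-only. The ordinary three-group model cannot carry them, and its covariate rule would delete the FT arm if it selected one.

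The benefit for the EEG outcome is uncertain. At d = 0.5 and 53 per arm it is up to 2 points of power for r up to 0.2, about 4 points at r = 0.3 and about 7 at r = 0.4. If the group means are evenly spaced, the contrast has only about 35% power unadjusted, and this adjustment does not repair that.

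A reader might infer more than the text supports:

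- *That Aim 2 uses no baseline information.* Parental demographics and neonatal chart data are pre-intervention and not VPT-only, and gestational age is named as a covariate.
- *That no three-group model could use T1.* The nested coding in step 4 of the working does.
- *That precision is certainly lost.* This depends on a correlation that the document does not give.
- *That the randomised contrast is biased without T1.* Leaving out a prognostic covariate costs efficiency and introduces no bias.

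The change is still worth making. It replaces outcome-driven selection with a fixed choice, on data already collected, at almost no cost.

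**What to change.** In Specific aim 2:

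1. Estimate VF versus CU in a model fitted to the two VPT arms, with one named T1 interaction score as a covariate fixed in advance, whatever its significance.
2. Adjust the T2 interaction rating for its own T1 value. This is where the gain is most likely, since T1 is a true baseline of that outcome.
3. Keep VPT-only variables (T1 rating, PSS-NICU) out of every model that contains FT. FT stays as a reference comparison.
4. State that T1 is recorded before any VF session and, where feasible, before the arm is disclosed to the family.
5. State how a missing T1 score is handled, for example by the mean over both VPT arms, so that no randomised dyad is lost for want of a covariate.

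Cost: a few sentences and one degree of freedom, with no new data. The remaining risk is that T1 follows allocation. If knowledge of the arm affected behaviour on the T1 tape, adjusting for it would no longer be clean, which is why item 4 matters.
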